##### Vitamin D status

Vitamin D status will be assessed from dried blood spot samples at the same timepoints. 25-hydroxyvitamin D [25(OH)D] concentrations will be measured with a dried blood spot test kit (Vitamin D Test, NeoVos by SureScreen Health, Newcastle Upon Tyne, United Kingdom).

##### Feasibility, usability and acceptability

Usability of the LightUP app will be measured by the mHealth App Usability Questionnaire (MAUQ) [31] at endpoint. Acceptability of the app and wearable devices will be assessed using adapted versions of the Technology Acceptance Model (TAM) [32] and the Theoretical Framework of Acceptability (TFA) [33] questionnaires at endpoint. Qualitative feedback on participant experience, app usage behaviour and overall acceptability of the app will be obtained through a focus group discussion at endpoint assessment.

#### Time points for analysis

Primary and secondary outcomes will be analysed at baseline (week 4), mid-intervention (week 10), end of intervention (week 16) and follow-up (week 28), depending on the measure. Continuous monitoring outcomes (e.g. light exposure, actigraphy, mood diaries) will be aggregated into daily or weekly metrics as appropriate.

### Participant timeline

The participant timeline and flow through the study are visualised in *Supplementary Fig. 1*. Following eligibility screening, obtaining informed consent, and documenting sociodemographic and health characteristics at Week 1, participants undergo a 4-week baseline monitoring period (weeks 1–4). During this period, they wear the ActLumus light logger and Garmin Vivosmart 5 activity tracker.

Following the baseline monitoring period, participants undergo baseline assessments (week 4) and are randomised in a 1:1 ratio to either the intervention or comparator arm.

The intervention phase lasts 12 weeks (weeks 4–16). Participants in the intervention group use the LightUP mHealth app, which delivers personalised feedback, education and goal setting, while participants in the comparator group use the placebo version of the app that records but does not provide feedback. Both groups continue to wear the ActLumus logger and Garmin device throughout this period. An additional drop-in session is delivered at week 10 to reinforce adherence.

A follow-up period of 12 weeks (weeks 17–28) follows the intervention. During this time, participants no longer use the app but continue their usual monitoring and assessments. The follow-up includes a 2-week monitoring phase with both the ActLumus and Garmin devices to assess sustained changes in light exposure, sleep and circadian rhythms.

Assessments are scheduled at four key time points:

Week 4 – Baseline assessment (BL): sleep quality (PSQI), mood (BMIS), cognition (NIH Toolbox), frailty (five criteria), physical activity (PASE), body composition, vitamin D (25(OH)D)Week 10 – Midpoint assessment (MP): interim assessments of sleep, mood, cognition, frailty, physical activity, body composition and vitamin DWeek 16 – Endpoint assessment (EP): repeat assessments including usability (MAUQ), acceptability (TAM, TFA) questionnaires and qualitative post-trial discussionWeek 28 – Follow-up assessment (FU): repeat full assessments, including 2 weeks of device-based monitoring

### Data collection

Outcome data will be collected using a combination of wearable devices, validated questionnaires, cognitive tests and clinical assessments as outlined in the Outcomes section of this protocol. Light exposure is measured continuously using the ActLumus pendant logger, while rest-activity cycles, sleep and physical activity are recorded using the Garmin Vivosmart 5 tracker. As outlined in Outcomes, validated self-report instruments include the PSQI, BMIS, VAMS, NIH Toolbox cognitive tests and PASE. Frailty measures include grip strength, gait speed, weight loss, exhaustion and activity level. Body composition is assessed using BIA and vitamin D is measured using dried blood spot analysis. Usability and acceptability of the intervention are assessed using the MAUQ, adapted TAM and TFA survey.

To ensure quality, all assessors are trained and certified in administering the questionnaires and performance-based measures. Standard operating procedures are in place for device calibration, biosample handling and data transfer. Data is collected electronically using secure, tablet-based entry systems, with automatic checks for out-of-range or missing values.

Participant retention and completeness of data collection will be supported through regular check-ins, technical support for device use and reminder notifications via the app in both trial arms. Participants who discontinue the intervention will still be invited to complete outcome assessments at scheduled visits unless they withdraw consent entirely. Reasons for non-adherence (e.g. device discomfort, loss of interest) or non-retention (e.g. withdrawal, loss to follow-up) will be systematically documented.

### Data management

All study data will be entered into a secure, password-protected electronic database hosted on institutional servers. Data entry will be performed electronically, with built-in range checks, mandatory fields and double verification procedures for critical variables. Data from wearable devices and the mobile application will be automatically synchronised with the study server via encrypted data transfer. Bio sample results will be entered by laboratory staff following validation procedures.

Participant confidentiality will be preserved throughout the trial. Personal identifiers (e.g. name, contact details) will be collected separately from research data and stored in encrypted, access-restricted files accessible only to authorised study staff. Each participant will be assigned a unique study identification number, which will be used for all data collection and analysis. Wearable device and app data will be encrypted at rest and in transit and stored in compliance with the Singapore Personal Data Protection Act. All data shared with collaborators or made publicly available will be fully anonymised.

Data security will be ensured through role-based access controls, password-protected user accounts and regular system backups. The final locked dataset will be archived on secure institutional servers for a minimum of 10 years following study completion.

### Sample size

Based on power calculations conducted using existing light exposure data, anchored to the primary outcome of time above threshold (TAT), defined as time spent above 250 lx melanopic EDI during daytime (TAT_250_), we estimate that a sample size of 25 participants per group (i.e., 50 participants in total) is sufficient to detect a 20% change in light exposure metrics with 80% power, assuming a standard deviation of 0.2 and a two-sided alpha of 0.05.

These calculations were based on an existing dataset from Malaysia, derived from a previous study comparing light exposure patterns in Switzerland and Malaysia [34]. This dataset is the closest available approximation to our target study population in terms of geographic and lifestyle similarities. The sample size estimation is documented in full in the project GitHub repository (https://github.com/tscnlab/MurukesuEtAl_BMCGeriatr_2026; 10.5281/zenodo.17914996 archived on Zenodo).

In the Malaysian dataset, daily time spent above 250 lx melanopic EDI (TAT_250_) averaged approximately 98 min per day, with 490 daily observations nested within 19 participants. This hierarchical data structure was retained in the power analysis using a mixed-effects model specification of the form outcome ~ intervention + (intervention | participant ID). As the original dataset was modelled using a Poisson distribution, the same distributional assumption was applied when generating simulation data for the power analysis via bootstrapping.

The power analysis focused on three light exposure metrics derived from the Malaysia dataset, as these represent conceptually relevant aspects of daytime and evening light exposure targeted by the LightSPAN intervention:

Time above 1000 lx melanopic EDI during the daytime (TAT_1000_)Time above 250 lx melanopic EDI during the daytime (TAT_250_)Time below 10 lx melanopic EDI in the evening (TBT_10_)

All three metrics are relevant in the context of the project, with TAT_250_ designated as the primary outcome. Importantly, the required sample sizes were identical for all three metrics when evaluated in increments of five participants per group, and therefore the same sample size estimate applies to the primary outcome.

A 20% relative change, which defines the minimum detectable effect for the primary outcome (TAT_250_), in each of these metrics corresponds to approximately:

~ 9 min/day increase above 1000 lx melanopic EDI~ 20 min/day increase above 250 lx melanopic EDI~ 30 min/day reduction below 10 lx melanopic EDI in the evening

However, to account for:

Additional outcome domains such as sleep, mood and cognitive function, which may show greater variability or require larger sample sizes to detect meaningful effectsConsidering the intensive nature of the trial and to effectively account for potential dropouts, an expected attrition rate of 25–30%, which is typical in studies involving older adultsThe need for more robust, generalizable results across a wider population

We plan to recruit a total of 90 participants (45 per group). This allows for approximately 63–68 participants to complete the study, corresponding to 31–34 participants per group, even after accounting for attrition. The recruitment strategy is guided by findings from similar mHealth interventions involving older adults, where dropout rates tend to be higher due to factors such as technology challenges, health status and varying levels of digital literacy. Studies in this demographic [35, 36] have demonstrated that over-recruiting by approximately 25–30% is a best practice to ensure adequate sample sizes for meaningful data analysis. By aiming to recruit at least 90 participants, we align with research standards that suggest this number is sufficient for exploratory analysis of the intervention’s effectiveness and feasibility.

### Statistical analysis

#### Analysis population

Analyses will follow the intention-to-treat principle, including all randomised participants in their assigned groups. A per-protocol sensitivity analysis will be performed including only participants with high adherence (≥ 80% app engagement and valid device wear).

#### Primary outcome analysis

The primary endpoint is light exposure behaviour, operationalised as the mean daily time (minutes per day) spent above 250 lx melanopic EDI during daytime hours. Light exposure patterns will be analysed per individual using generalised linear mixed models (GLMMs). Daily TAT values will be entered into models including group assignment and assessment block/day-in-trial as fixed effects, with participant-level random effects to account for repeated daily measurements.

Based on prior analyses of TAT in a Malaysia–Switzerland light exposure study [34], Poisson and Gamma error distributions were identified as an appropriate fit for mixed-effects modelling and are therefore used for all analyses with TAT as the dependent variable.

The full model in Wilkinson notation will follow this specification:$$\begin{aligned}&\:\mathrm{Outcome\:variable}\:\sim\:\mathrm{group}*\mathrm{assessment\:block}\\&+\mathrm{sex}+\mathrm{age}+\left(\mathrm{assessment\:block}\right|\mathrm{participant})\:\end{aligned}$$

Model diagnostics will include visual checks for homoscedasticity, normality of residuals and random effects, and their location at zero. Baseline characteristics, including sociodemographic variables, health status, and baseline outcome measures, will be summarised descriptively by study group, and selected variables may be included as covariates in secondary or exploratory analyses where appropriate.

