##### Allocation concealment and implementation

To guarantee allocation concealment, the allocation sequence will be securely implemented by a research team member who is not in direct contact with the participants.

Participant enrolment is conducted by trained research staff at the partner Active Ageing Centres. Group assignment is performed only after eligibility confirmation and completion of the baseline observation phase. The random allocation sequence is generated by an independent statistician and stored within a secure, central, web-based randomisation module managed by the data management team. Enrolling staff request assignment through this system; the system releases the allocation only at the point of randomisation. Personnel responsible for enrolment and those delivering study procedures have no access to the randomisation list or block details. The master sequence file is access-restricted (statistician and data manager only) and kept on an encrypted server with audit logs.

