### Outcomes

#### Primary outcome

The primary outcome is the effectiveness of the LightUP app in improving light exposure behaviour in older adults. This will be assessed using data from the ActLumus wearable light logger (ActLumus, Condor Instruments; São Paolo, Brazil) across the 4-week baseline, the 12-week intervention and the 2-week follow-up monitoring period. The primary analysis metric is the mean daily time (minutes per day) above 250 lx melanopic equivalent daylight illuminance (melanopic EDI) during daytime hours. Changes will be calculated relative to baseline and both short-term effects (during the 12-week intervention) and longer-term effects (during follow-up) will be examined.

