#### Secondary outcomes analyses

Secondary endpoints include outcomes spanning sleep, circadian rhythms, mood, cognition, frailty, physical activity, body composition, vitamin D status, and feasibility-related measures, assessed at BL, MP, EP, and FU, depending on the measure.

Quantitative differences across assessment time points will be examined using GLMMs or linear mixed-effects models, depending on the distributional properties of each outcome. Models will include group, assessment block, and group-by-assessment block interaction as fixed effects, with participant included as a random effect to account for repeated measures.

Statistical significance will be assessed using a two-sided alpha level of 0.05. p-values will be calculated using likelihood ratio tests comparing models with and without the parameter of interest. Unstandardised effect sizes (beta coefficients) will be reported. A false discovery rate correction will be applied within each branch of secondary outcome analyses, based on the number of models or tests performed within that branch.

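### Free improvement: the primary model gives each arm its own baseline mean although baseline precedes randomisation, which is valid but generally less precise than it need be

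*Protocol article*

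**What the plan says.** Under Primary outcome analysis, daily time above 250 lx melanopic EDI (TAT250) is the outcome variable: "Daily TAT values will be entered into models including group assignment and assessment block/day-in-trial as fixed effects", with participant-level random effects. That sentence does not show an interaction. The formula introduced by "The full model in Wilkinson notation will follow this specification" does: `group*assessment block + sex + age + (assessment block | participant)`.

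The baseline days are rows of outcome data, because the Primary outcome section assesses light exposure "across the 4-week baseline, the 12-week intervention and the 2-week follow-up monitoring period". The same section sets the target: "Changes will be calculated relative to baseline".

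On timing, Allocation concealment and implementation says: "Group assignment is performed only after eligibility confirmation and completion of the baseline observation phase". Study design and Participant timeline agree.

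Baseline outcome measures are summarised by arm, and "selected variables may be included as covariates in secondary or exploratory analyses where appropriate". The primary model therefore has no baseline covariate and no equal-baseline constraint.

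Secondary outcomes analyses repeats the structure: "Models will include group, assessment block, and group-by-assessment block interaction as fixed effects, with participant included as a random effect".

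**The concern.** Crossing group with block expands to group + block + group:block. With baseline as the reference block, the group main effect is the baseline difference between arms. All baseline data precede allocation, so the expected value of that difference is zero by design. The model nevertheless estimates it freely and subtracts the estimate from the later difference.

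The resulting contrast is a difference in mean changes. It subtracts the whole observed baseline difference, whereas the best predictor would subtract only the part that persists into the later block. Sex and age do not make up for this. They enter as main effects, are constant within a participant, and so cancel from a change contrast.

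At stake is precision on the primary comparison and on the secondary ones. Under Sample size the sponsor says that sleep, mood and cognition may need larger samples, and under Limitations it names attrition as a threat to power.

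**Working it through.** **Inputs from the protocol.** Model formula, baseline block, timing of allocation and 1:1 ratio as above; 28 baseline days and 84 intervention days per participant (4 and 12 weeks); 31–34 completers per group (Sample size). The protocol gives no baseline-to-later correlation and no variance components, so rho and the variance ratio below are assumptions.

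**The plan's own figure.** Sample size states 25 per group for a 20% change, SD 0.2, 80% power, two-sided 0.05. The two-sample formula n = 2(1.96 + 0.84)² × 0.2²/delta² gives 16 per group for delta = 0.20 and 19 for delta = log 1.2. With a change-score variance of 2 × 0.2² × (1 − rho), it reaches 25 on the log scale only at an assumed rho of about 0.35. The 25 is therefore not reproduced by closed form. It came from a mixed-model simulation on data not shown here, so this does not prove it wrong, and it yields no usable rho.

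**Step 1: is the contrast a difference in changes?** A linear mixed model of the stated form, with random block effects, sex and age, was fitted to balanced simulated data. The group-by-block estimate was 0.3054 and the difference in mean changes was 0.3054. In the log-link GLMM planned here the equivalence is close, not exact.

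**Step 2: variance.** Let k = SD(later)/SD(baseline), in units of the baseline variance and per participant.

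- Free baseline means: 1 + k² − 2·rho·k
- Common baseline mean or baseline-adjusted: k²(1 − rho²)
- Difference: (1 − rho·k)², which is never negative and is zero only when rho·k = 1
- Share saved: (1 − rho·k)²/(1 + k² − 2·rho·k), which is (1 − rho)/2 when k = 1

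| k | rho 0.5 | rho 0.7 | rho 0.8 | rho 0.9 |
|---|---|---|---|---|
| 0.8 | 43% | 37% | 36% | 39% |
| 1 | 25% | 15% | 10% | 5% |
| 1.25 | 11% | 2% | 0% | 5% |

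Example with k = 1 and rho = 0.7: 2(1 − 0.7) = 0.60 against 1 − 0.49 = 0.51, and 1 − 0.51/0.60 = 15%.

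**Step 3: checks.** In one linear fit without sex and age, removing the baseline difference cut the standard error of the contrast from 0.186 to 0.165, a variance saving of 1 − (0.165/0.186)², about 21–22%. In simulated Poisson counts with 34 per arm, analysed on the log scale, both estimators were unbiased. The savings were 36%, 26%, 16%, 7% and 5% at rho 0.3, 0.5, 0.65, 0.8 and 0.9, against 35%, 25%, 17.5%, 10% and 5% from the formula.

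**Step 4: averaging over many days.** Assume random block effects (SD 0.2) independent of the intercepts, intercept SD 0.3–0.8 and day-level SD 0.8–1.2, with 28 and 84 days. The correlation of block means is then 0.62 to 0.95 and the saving about 1% to 17%.

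**Step 5: in participants.** With k = 1, multiply 31–34 completers per group by 2/(1 + rho). At rho 0.9 they count as about 33–36, at 0.8 as 34–38, and at 0.5 as 41–45.

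**The case against.** The strongest reply is that nothing here is wrong. The planned contrast is unbiased over randomisations, and it answers the question the protocol asks, a change relative to baseline. That stands, and it is why this is a recommendation and not an error.

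Three stronger readings are tempting, and the documents support none of them.

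- A reader might infer that chance baseline imbalance biases the result. It does not. Conditional on a given imbalance the estimate is shifted, but across randomisations this appears as extra variance.
- A reader might infer a fixed loss, such as 10–25% of the variance. That range needs rho between 0.5 and 0.8 and equal variances, and the protocol states neither.
- A reader might infer that the primary comparison is underpowered as a result. The protocol's only SD is 0.2, on an unstated scale. If it is read as the SD of change, with 32 per arm, the standard error is 0.2 × √(2/32) = 0.05. Power is then already about 95% (delta = log 1.2) or 98% (delta = 0.20). A larger change SD would give less, but the protocol provides none.

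It can also be said that the time coding is open between assessment block and day-in-trial, that no single primary contrast is named, and that a separate analysis plan will follow. This is partly right: the change-score reading applies to categorical blocks. But the displayed formula uses assessment block and is presented as the full model, and the same section confines optional covariates to secondary or exploratory analyses. The protocol has therefore fixed the less efficient form.

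**Conclusion.** The point holds as a free gain in efficiency. The primary model leaves the baseline means free although the design makes them equal in expectation. The group-by-block contrast therefore generally has a larger variance than the same data allow. In large samples the constrained analysis cannot do worse, and it gains nothing only when rho·k = 1.

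The size cannot be fixed from the documents. With equal variances it is (1 − rho)/2; across the assumed inputs it runs from about 0% to over 35%. For the primary outcome, block means average many days, which tends to raise rho, so the gain is probably at the small end and may be only a few percent. Several secondary outcomes, such as PSQI and the cognitive tests, have a single week-4 value. There rho is plausibly lower and the gain larger.

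The conclusion rests on categorical blocks with baseline as reference, and on a log-link GLMM behaving nearly like its linear counterpart, which the Poisson simulation supports.

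**What to change.** Constrain the baseline mean to be common to both arms. Replace the crossed term with block plus an explicit indicator for each post-baseline block, equal to 1 for active-arm participants in that block and 0 otherwise. Keep sex, age and the participant-level block random effects. For three blocks this gives 3 block means and 2 treatment terms, 5 parameters in place of 6.

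Do not write it as block + group:block with factors. That formula still spans all 2 × 3 = 6 cell means, as the crossed term does, so the baseline means stay free.

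An alternative is to model the post-baseline days only, with the participant's baseline mean TAT250 as a covariate on the log (link) scale. A covariate in raw minutes is a different model under a log link.

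Apply the same change to every secondary outcome with a week-4 baseline value.

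The cost is one formula and its wording in the analysis plan, which the protocol says will be finalised before data analysis. Protocol amendments lists changes to analyses among the substantial ones, so that route applies if the change is classed that way. No new data are needed.
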